## 2. Sample size

- **Initial a priori calculation:** 350 participants required to detect a standardized mean difference of Cohen's  $d = 0.50$  (mean difference = 3.5; SD = 7), with 90% power, 2-sided  $\alpha = 0.05$ , and 30% dropout.

## 3. Analysis populations

- **Intention-to-treat (ITT):** All randomized participants analyzed according to their assigned group, regardless of adherence. The ITT population will form the primary analysis set.
- **Per-protocol (PP):** All participants who adhere to the intervention (>2 of 6 modules completed in TG-iConquerFear, or equivalent engagement with control condition). PP analyses will be performed to examine the robustness of ITT findings.
- **Exploratory subgroups:** Completers (6 modules) versus partial completers (2–5 modules). Analyses will also explore differences in demographic and psychosocial characteristics between subgroups.

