**Part 2 b, randomization**

*If randomized to augmented TAU:* The control group is described as “augmented” as the diagnostic telephone interview exceeds standard treatment. Furthermore, if randomized to augmented TAU the information letter (appendix 7. Informationsbrev) send to E-boks will include a reference to a website with a non-guided, publicly available E-learning program in cancer rehabilitation hosted by the Region of Central Jutland (livogkraeft.rm.dk). The website includes, besides a written material, self-help instructions for meditation. Use of the website will not be monitored.

*If randomized to TG-iConquerFear:* The information letter (Appendix 7. Informationsbrev) will contain a link to enter the platform directly. The assigned therapist will be informed simultaneously.

Both groups will follow standard surveillance according to national guidelines for cancer recurrence at a surgical or oncological department, which may include colonoscopy and/or CT scans. The municipality is responsible for rehabilitation and offers limited access to physical exercise, yoga, dieticians, psychologists, sexologists etc.

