### **Part 4, intervention**

The theoretical frame of iConquerFear[29] is based on the Common-Sense Model (CSM) of illness, the Self-Regulatory Executive Function model (S-REF; targets metacognitions) and Relational Frame Theory (RFT; theoretical basis for Acceptance and Commitment Therapy). The intervention includes elements of attention training, increasing metacognitive awareness, acceptance & mindfulness, promotion of expedient screening behaviour, and values-based goal setting. The platform is accessed through secure log-on and comprises 5 modules containing educational text, interactive exercises, short videos featuring doctors, therapists and patients' perspectives, see Fig. 3.

The Australian version of iConquerFear is completely self-directed.

The Danish version of iConquerFear will contain a messenger-function on the intervention dashboard, allowing the participant and therapist to communicate asynchronously (TG-iConquerFear). The participant is guided through the sessions by minimum weekly contact with an experienced therapist. The therapist will motivate, answer questions and give feedback on written material and exercises. The amount of contact will be recorded and explored as a moderator of intervention efficacy. Should any cancer-related questions occur, an oncologist or surgeon will be involved as a consultant to the therapists.

The programme can monitor adherence, dropouts and track log-ins and activity. A purpose-developed single-item questionnaire within the TG-iConquerFear will each week ask for level of engagement[47]. Participants who do not adhere to, or withdraw from, the intervention will be contacted by telephone and asked why. These participants will be asked if they would be willing to complete a post-intervention assessment and all follow-up assessments to aid intervention evaluation. Therapist assistance is scheduled to last 10 weeks, but the participants will have free access to the platform for another 6 months.

In case of recurrence during the 10 weeks of intervention, the participant will be excluded from analysis, but may continue in the programme.

Fig. 3, iConquerFear curriculum content

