| 3. Detached mindfulness                                                                                                                             | 
 
• Introduction to Detached Mindfulness (Therapist videos)
 
• Demonstration of Detached Mindfulness exercises (Animated videos, therapist feedback)
 
                                                                                                                                                                |
| 4. Learning to live well and manage worry                                                                                                           | 
 
• Psycho-education regarding appropriate threat monitoring behaviours (Annotated PowerPoint video)
 
• Assessing compliance with follow-up & self-examination recommendations (Interactive exercise with personalised feedback)
 
• Worry management techniques (Textual overview and downloadable PDF)
 
 |
| 5. Treatment summary and relapse prevention                                                                                                         | 
 
• Assessment and feedback on change in FCR symptoms during treatment (therapist feedback)
 
• Consolidation of newly acquired strategies for managing FCR through relapse prevention (therapist feedback and downloadable action plan)
 
                                                                             |
| Features common across all modules include: Write to your therapist, interactive exercises, downloadable handouts, progress graphs and safety plan. |                                                                                                                                                                                                                                                                                                                                                                             |

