### Update 10 Jan 2025

#### Deviations from SAP

Several analyses specified in the statistical analysis plan were not conducted due to limitations in sample size and data availability.

- Per-protocol analyses were not performed, as the five participants classified as passive users (<2 modules completed) did not contribute outcome data, precluding meaningful subgroup comparison.
- Mediator analyses (eg, illness uncertainty, perceived risk of recurrence, negative beliefs about worry) were not conducted because of insufficient statistical power.
- Predictor analyses of demographic and clinical moderators (eg, age, gender, disease stage, treatment type) were omitted for the same reason.
- Economic analyses, originally planned using registry data, were not undertaken due to lack of power and feasibility constraints.

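### SAP section 3 counts adherence on 6 modules where the protocol describes 5, and its per-protocol criterion for controls is undefined and has no data source

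*Combined protocol and SAP*

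**What the plan says.** **Module count, protocol.** Part 4, intervention says the platform "comprises 5 modules containing educational text, interactive exercises, short videos". The curriculum table in the same section (Fig. 3) numbers the modules 1 to 5, and the last row is "5. Treatment summary and relapse prevention".

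**Module count, SAP.** Section 3 (Analysis populations) defines the per-protocol set as ">2 of 6 modules completed in TG-iConquerFear, or equivalent engagement with control condition". It then defines an exploratory split, "Completers (6 modules) versus partial completers (2–5 modules", and plans to compare the characteristics of the two subgroups.

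**Adherence data.** For the intervention arm, Part 4 says: "The programme can monitor adherence, dropouts and track log-ins and activity". For the control arm, Part 2 b, randomization says of the e-learning site offered to controls: "Use of the website will not be monitored".

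**Role of each set.** SAP section 3 makes ITT the primary analysis set, gives the per-protocol set the role of a robustness check, and calls the completer split exploratory.

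**What was later dropped.** The update of 10 January 2025 (Deviations from SAP) says the per-protocol analyses were not done because "the five participants classified as passive users (<2 modules completed) did not contribute outcome data, precluding meaningful subgroup comparison". It also lists the mediator, predictor and economic analyses as not done. It does not mention the completer comparison, the number of modules or the control criterion.

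**The concern.** An adherence definition has to be one that can be applied to the data the trial collects. Three parts of this one raise doubt.

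- The completer threshold lies above the number of modules in the protocol, so a participant who does everything offered may fall in the wrong subgroup.
- Controls must show a level of engagement that is not defined and for which no measurement is planned.
- The cut-offs for per-protocol, partial completer and passive user do not meet at the same point.

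At stake is whether a reported adherence subgroup can be traced to the plan, and whether a per-protocol result could serve the purpose the SAP gives it. The completer comparison matters most in practice, because nothing in the documents says it was abandoned.

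**Working it through.** **Step 1. Module count.** The SAP's figure is 6, used both as the per-protocol denominator and as the completer threshold. Counting the rows of the protocol's curriculum table gives 5, which agrees with the protocol's text. The figure of 6 is not reproduced, and neither document describes a sixth module.

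**Step 2. Apply the written rules to each possible count.** The rules are: per-protocol if more than 2; partial completer if 2 to 5; completer if 6 (all from SAP section 3); passive user if fewer than 2 (January 2025 update).

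| Modules completed | Per-protocol (>2) | Exploratory subgroup | Passive (<2) |
|---|---|---|---|
| 0 | no | none | yes |
| 1 | no | none | yes |
| 2 | no | partial | no |
| 3 | yes | partial | no |
| 4 | yes | partial | no |
| 5 | yes | partial | no |
| 6 (only if a sixth module exists) | yes | completer | no |

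Three results follow.

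- With a maximum of 5, the last row cannot occur. A participant with 5 of 5 is a partial completer, and the completer group has no possible members. With a maximum of 6, the group can have members.
- The intervention-arm per-protocol rule does not depend on the denominator. More than 2 selects the same people among counts 0 to 5 whether the total is 5 or 6.
- A count of exactly 2 is outside the per-protocol set, inside the partial group and outside the passive group. The per-protocol rule starts at 3; the other two definitions place their boundary at 2.

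**Step 3. Apply the per-protocol rule to controls.** The rule needs a measure of engagement and a threshold equivalent to 3 or more modules. The SAP gives no threshold, and the protocol rules out monitoring of the control site. No control can therefore be classified one by one, which leaves two options:

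- drop all controls, and there is no comparison;
- keep all controls, and intervention participants selected for adherence after randomisation are compared with unselected controls.

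In the second case any difference mixes the treatment effect with whatever distinguishes people who persist. Agreement or disagreement with ITT would then say little about the robustness of ITT. This holds for 5 modules or 6.

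**Step 4. Compare the 2025 reason with the rule.** The update refers to five participants with 0 or 1 module. The SAP rule removes counts 0, 1 and 2. The two agree on who leaves the intervention arm only if nobody completed exactly 2. The documents do not report that number.

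**The case against.** The case for leaving this alone is a reasonable one. ITT is primary, the per-protocol set is a supporting check, the completer split is exploratory, and the per-protocol analysis was not run, so no confounded contrast is reported. The protocol text is also prospective: further adjustment of the platform and a pilot were still to come. The SAP uses 6 consistently, and on a 6-module platform the groups below 2, 2 to 5, and 6 partition cleanly. Per-protocol membership and the exploratory split are separate classifications, so a partial completer outside the per-protocol set is not a contradiction in itself.

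Most of this stands, and it limits the point. It does not remove the mismatch in module count, the control criterion that cannot be applied, or the one-module difference between boundaries.

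A reader might also infer more than the documents support:

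- *That none of the adherence groups can be formed.* The intervention-arm per-protocol and partial groups can be, from platform tracking, and the update reports that passive users were classified.
- *That the completer group is empty as a matter of fact.* This depends on 5 modules having been delivered, which the documents do not settle.
- *That the hypothesis of high engagement in some participants cannot be examined.* SAP section 4 makes modules completed and communication with the therapist outcomes in their own right, section 5.5 plans to describe modules completed, and the protocol adds a weekly engagement item. None of these needs the completer label.
- *That the reason given in January 2025 is false.* With the number at exactly 2 modules unreported, the documents show only that the passive cut-off differs from the SAP rule.

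**Conclusion.** The definitions in SAP section 3 need correcting; the trial's primary result does not depend on them.

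- **Module count.** 5 in the protocol against 6 in the SAP is a plain contradiction. On the assumption that 5 were delivered, every full finisher is labelled partial, the completer group has 0 possible members, and the exploratory completer comparison cannot be run as written. If 6 were delivered, the protocol's description is the text to correct.
- **Control criterion.** Undefined and without a data source under either count. A per-protocol contrast that kept all controls would select for adherence in one arm only and could not do the job the SAP assigns to it.
- **Cut-offs.** Misaligned by one module, affecting participants with exactly 2; how many there are is not reported.

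The correction is worth making because it costs little and because the completer comparison is not listed among the abandoned analyses.

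**What to change.** 1. Reconcile the number of modules between the protocol (Part 4, intervention) and SAP section 3, and define a completer as someone who finishes all modules delivered.
2. Use one boundary for the per-protocol, partial and passive definitions.
3. Delete the control half of the per-protocol rule. Do not present a per-protocol contrast as a robustness check of ITT; describe adherence within the intervention arm only.
4. State in the January 2025 update which adherence cut-off was applied.

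These are changes of wording, and the platform is already set up to track activity. The cost is giving up a per-protocol comparison that could not have been interpreted as planned.

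A complier-average causal effect, with randomised arm as instrument, is optional. It needs no adherence data from controls, but it is more than a routine extra model. The passive users contributed no outcomes and SAP section 6 plans no imputation, so it would need stated assumptions about those missing outcomes. It would also need an exclusion assumption, which is strained because participants below any module cut-off may still have received some modules and therapist contact.

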## 4. Outcomes

### Primary outcome

- Change in FCRI total score from baseline to 3 months.

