## EVALUATION

### Primary outcome measure

The primary outcome measure is the 3 month follow-up (T1) total score on the recently validated Danish version of the FCRI [13]. The FCRI is a 42-item self-report measure that includes subscales assessing FCR triggers, severity, psychological distress, functioning impairments, insight, reassurance, and coping strategies [48]. The FCRI has demonstrated high: internal consistency ( $\alpha=0.96$ ) [49], interclass correlation (0.84) [13] and convergent validity in large heterogeneous cancer survivor samples. Respondents rate the degree to which symptoms/issues affected them over the past month on a Likert scale ranging from 0 ('not at all' or 'never') to 4 ('a great deal' or 'all the time'). While there are potential issues with aggregating FCRI subscales [50], total FCRI score will be used as the dependent variable, as it closely reflects proposed features of clinically significant FCR; namely related distress, functional impact, and maladaptive coping[2], rather than the level of fear indicated by the FCRI-SF [50, 51]. Total scores can range from 0-168; higher scores indicate greater FCR morbidity. Level of FCR will be measured post-treatment (T0) and at follow-up after 3 (T1) and 6 (T2) months. Long-term effect will be evaluated after one year (T3). All electronic questionnaires will be sent out automatically through RedCAP.

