### Statistical analysis

A flowchart of participants and dropouts following the CONSORT guidelines will be drawn.

STATA will be used for all statistical analyses. All statistical tests will be two-sided (level of significance = 0.05).  $\chi^2$ -tests will be performed on all follow-up data to analyse proportions of participants above or below the clinical cut-off.

The influence of the intervention will be analysed for the primary outcome and for all secondary outcomes. Linear mixed effects models will be used to analyse longitudinal differences between intervention and control group. Association with functional disorders (health anxiety and bodily distress symptom) and psychiatric disorders (anxiety and depression) will be evaluated with adjusted and unadjusted linear regressions analyses on baseline data.

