### Primary hypothesis

- TG-iConquerFear will result in a greater reduction in FCRI total score at 3 months post-intervention compared with control.

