### 5.2 Primary analysis

- Within-group changes from baseline to follow-up assessed with paired *t*-tests.
- Between-group differences in mean change scores tested using 2-sample *t*-tests (or non-parametric equivalent if assumptions violated).
- Effect size (Cohen's *d*) and 95% CI reported for between-group differences at 3 months.

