### 5.3 Secondary analyses

- Continuous secondary outcomes analyzed using paired *t*-tests and between-group comparisons of change scores.
- Longitudinal analyses across baseline, 1/2, 3, and 6 months using **linear mixed-effects models**, with fixed effects for group, time, and interaction, and random intercepts for subjects.
- Proportions above/below clinical cut-offs analyzed using  **$\chi^2$  tests**.
- Reliable and clinically significant change indices calculated.

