## 7. Multiplicity

- No formal adjustments planned. Secondary and exploratory analyses considered hypothesis-generating.

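### The protocol takes the 3-month FCRI score as primary and the SAP takes the change from baseline; nothing says which governs, and free choice between the two would raise the false-positive rate to about 9%

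*Combined protocol and SAP*

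**What the plan says.** Protocol, Primary outcome measure: "The primary outcome measure is the 3 month follow-up (T1) total score on the recently validated Danish version of the FCRI". The variable is the score at that visit, not a difference from baseline.

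Protocol, Statistical analysis: "The influence of the intervention will be analysed for the primary outcome and for all secondary outcomes". The next sentence reads "Linear mixed effects models will be used to analyse longitudinal differences between intervention and control group". Neither sentence calls the mixed model the primary test or names a contrast at T1. The only test the protocol ties to the primary outcome is the two-sided t-test assumed in Power calculation.

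SAP, section 1, Primary hypothesis: "TG-iConquerFear will result in a greater reduction in FCRI total score at 3 months post-intervention compared with control".

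SAP, section 4, Primary outcome: "Change in FCRI total score from baseline to 3 months".

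SAP, section 5.2 Primary analysis: "Between-group differences in mean change scores tested using 2-sample" t-tests, with a non-parametric test if the assumptions fail.

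SAP, section 5.3 Secondary analyses: "Longitudinal analyses across baseline, 1/2, 3, and 6 months using" linear mixed-effects models. Here the mixed model is plainly secondary.

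SAP, section 7: "No formal adjustments planned". Secondary and exploratory results are treated as hypothesis-generating.

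No sentence in either part gives one text precedence. The SAP update of 10 January 2025 lists per-protocol, mediator, predictor and economic analyses as not done. It does not mention that the primary variable moved from score to change.

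**The concern.** The T1 score and the change from baseline are different variables, and their tests can disagree. With the 68 participants of the September 2023 update, a chance imbalance in baseline FCRI can make one test significant and the other not. As the document stands, a T1-score result can be called primary by pointing to the protocol, and a change-score result by pointing to the SAP. If that choice were made after seeing both, the nominal two-sided 5% would no longer describe the risk of a false claim. A reader of the trial report could not tell from the plan which result was meant to decide.

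**Working it through.** **Inputs**
- Two-sided significance level 0.05 (protocol, Statistical analysis; SAP section 8). This is the only error rate the plan states.
- 1:1 allocation (protocol, RCT); 68 participants and 20% dropout (SAP update September 2023). Evaluable per arm: 68 × 0.80 / 2 = 27.2, taken as 27.
- Correlation r between baseline and T1 FCRI: not in the documents. Assumed 0.3 to 0.84. The protocol quotes an interclass correlation of 0.84 for the Danish FCRI, but from a validation study, so it serves only as an upper value here.
- Equal variance σ² at baseline and T1: assumed.

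**Step 1. How closely the two tests agree.** Let B be the baseline score and Y the T1 score.
- Cov(Y, Y − B) = σ²(1 − r)
- Var(Y − B) = 2σ²(1 − r)
- Correlation of the two test statistics = (1 − r) / √(2(1 − r)) = √((1 − r)/2)

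**Step 2. Chance under the null that at least one is significant.** With Z₁ and Z₂ bivariate normal with that correlation, the rate is 1 − P(|Z₁| < 1.96 and |Z₂| < 1.96).

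| r | correlation of tests | either test p < 0.05 |
|---|---|---|
| 0.3 | 0.59 | 8.8% |
| 0.5 | 0.50 | 9.1% |
| 0.7 | 0.39 | 9.4% |
| 0.84 | 0.28 | 9.5% |

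The ceiling for two independent tests is 1 − 0.95² = 9.75%. Simulation with 27 per arm and 100,000 trials per value of r gave 8.7%, 8.9%, 9.3% and 9.4%, with each single test at about 4.9% to 5.1%. The result hardly depends on r.

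**Step 3. The SAP alone.** One t-test on change gives about 5%. Taking the better of the t-test and the rank test on change gives about 6% (simulated, 27 per arm).

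**Step 4. The mixed model against the change-score t-test.** With complete balanced data, the group-by-time estimate at T1 equals the difference in mean change, so the two tests nearly coincide. Simulated rates for either being significant, using a random-intercept model over four visits:
- 4.9% to 5.8% with complete data and equal correlation between visits
- 6.1% to 6.9% with 20% to 30% dropout
- 6.9% to 7.6% when correlation decays between visits (AR(1))

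So the mixed model is not the main source of the problem; score versus change is.

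**Step 5. Why adjusting for baseline removes the conflict.** Fit Y = a + b·arm + c·B. Subtracting B from both sides gives Y − B = a + b·arm + (c − 1)·B. The arm coefficient b, its standard error and its p-value are unchanged, so score and change become the same test.

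**The case against.** The best defence is that the SAP, read alone, is clear. It has one primary outcome, an intention-to-treat primary set, one between-group test with a rank fallback, and the mixed model among the secondary analyses. It is the dedicated analysis document for this trial, so a reader would normally follow it. That stands, and it is why about 5% to 6% is the right figure under the SAP. What it does not answer is that the protocol's definition sits in the same combined document, is not withdrawn, and is missing from the list of deviations.

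A T1-score t-test is also nowhere listed as an analysis. That is true as well. It comes from putting the protocol's primary variable together with the t-test of its power calculation. This is a fair reading but an inference, so the 9% must stay conditional.

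A reader might infer two stronger points. One is that the protocol makes the mixed model the deciding test and the SAP demotes it. The protocol never labels it primary, and its power calculation assumes a t-test. The other is that several deciding tests exist at full alpha and the error rate is about 12% to 13%. Figures of that size appear in simulation only when the mixed-model T1 contrast and the joint group-by-time test are added to the two t-tests. No section names either of them as primary.

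Finally, the January 2025 update speaks of participants who gave no outcome data, which suggests that outcomes were already in hand. A new primary model chosen now would be a late choice. This objection stands and shapes the fix.

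**Conclusion.** The contradiction is real. The protocol and the SAP define the primary variable differently, neither is given precedence, and the change is not recorded. The consequence is limited. Under the SAP alone the false-positive rate is about 5%, or about 6% with the rank fallback used opportunistically. It reaches 8.8% to 9.5% only if a T1-score t-test counts as a permitted primary analysis and the better of the two results is reported. That range assumes r between 0.3 and 0.84, equal variances at the two visits, and complete pairs. Nothing in the documents shows that such a choice was made. The point should be corrected because the ambiguity bears on the one result that decides the trial.

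**What to change.** In SAP sections 4 and 5.2:
- State that the SAP governs the primary analysis and replaces the protocol's Primary outcome measure and Statistical analysis text on this point.
- Name one deciding test: one variable, the T1 visit, one model, one two-sided p-value at 0.05. Preferably this is a linear model of T1 FCRI total on arm with baseline FCRI as covariate, which makes the two definitions coincide.
- Label the T1-score t-test, change-score t-test, rank test and mixed-model tests as sensitivity analyses that cannot alter the conclusion.
- Add the protocol-to-SAP change of primary variable to the January 2025 deviations.

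If outcome data had been seen before this is settled, disclose the baseline-adjusted model as a late change and report it next to the SAP's change-score t-test.

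The cost is a few lines of text and one entry in the deviations list. Baseline FCRI is already collected, so no further data or participants are needed. The sponsor gives up the choice between primary results and, if the change is late, must carry that disclosure in the report.
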